##### Pulmonary Function Tests

Pulmonary function tests will be assessed by the following spirometry parameters: forced expiratory volume in the first second of expiration (FEV_1_), forced vital capacity (FVC), FEV_1_/FVC and vital capacity (VC), and reported as a percentage of the predicted value. A spirometer (microQuark, COSMED) will be used for these measurements, which will be performed at baseline and at 30 days post-randomization.

##### Quality of Life

Questionnaires including the 36-item short-form (SF-36) (16), Modified Medical Research Council (MMRC) dyspnoea scale (17) and EQ-5D-3L (18) will be used for the assessment of quality of life in our participants. Both interviews will be performed twice, first at baseline and again at 30 days post-randomization.

### Laboratory Testing

Routine clinical parameters, including laboratory tests such as electrolytes, troponin I/T, creatine kinase-MB (CK-MB), blood lipid, serum creatinine, and other clinical routine parameters examination will be performed within 12 h after admission. The eGFR will be assessed with the four-variable modification of diet in renal disease equation for Chinese patients (19). An additional 4 mL venous blood sample will be collected, and the isolated serum will be stored at −80°C for a future mechanism study.

### Assessment and Reporting of Adverse Events

Adverse events including all-cause death, recurrence of myocardial infarction, stroke, stent thrombosis, angina, dyspnea, acute heart failure, arrhythmia, and other unforeseeable incidents will be recorded in detail during both the in-hospital and follow-up periods. The reporting and documentation of adverse events will be classified as IMT-related or non-IMT-related. This safety analysis will be conducted at the end of our research among patients who had at least 1 day of outpatient safety data.

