### Study Oversight

A specific data safety committee has been guaranteed for the current research, consisting of two cardiologists and one statistician. The cardiologists will be responsible for the review of the in-hospital course and follow-up adverse events of the participants. Then, a safety analysis will be conducted by the statistician at the time the 20th participant is randomized, and the data will be divided into IMT-associated events or non-IMT-associated events.

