### Invention: IMT

For the IMT group, IMT will be performed for 15 min *per session*, twice a day, with an initial load of 30% of MIP using a threshold inspiratory muscle trainer (c-type, Shengchang medical equipment factory, Yuyao City, China). During the hospital period, the resistance will increase incrementally, based on the rate of perceived exertion scored on the Borg scale (11). If the rate of perceived exertion is <5, the resistance of the inspiratory threshold trainer will then be increase incrementally by 5%. To facilitate training for participants, the load for home-based IMT training will be set at the highest training load achieved while the patient was in hospital. All of the participants will be required to complete maneuvers in the seated position during training, wearing nose-clips. IMT will be performed every day from 12 to 24 h after primary PCI and the final session will be performed 30 days post-randomization. Participants in the control group will receive standard care after primary PCI according to the current clinical practice guidelines (12), which included risk stratification, continuous monitoring and specific nursing. And we also encourage an early ambulation, based on the complications, symptoms, and capacity.

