### Follow-Up

Participants will be followed by two experienced researchers every week through phone interviews after discharge. Details of IMT will be documented, quality assessment will be performed, and any reported adverse events will be followed up, with assistance provided if necessary. All of the participants will be asked to return to the clinic for follow-up visits at 30 days post-randomization.

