#### Secondary Endpoints

##### Feasibility

Adverse events, heart rate, systolic blood pressure, diastolic blood pressure, and oxyhemoglobin saturation of patients during training while in hospital will be recorded. In addition, the workloads of MIP and the Borg scores will be recorded after every day of training in the hospital. The satisfaction of patients in the IMT group will be evaluated using a questionnaire at discharge and again at 30 days post-randomization (Supplementary Appendix 1).

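### In-hospital training sessions give the IMT arm an extra twice-daily layer of adverse-event and vital-sign recording, so minor events may be ascertained more intensively there than in controls

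*Protocol article*

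**What the plan says.** Three parts of the protocol article bear on this.

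- **General rule.** Assessment and Reporting of Adverse Events lists events from death to angina, dyspnea and arrhythmia and says they "will be recorded in detail during both the in-hospital and follow-up periods". No arm is named. It then states: "The reporting and documentation of adverse events will be classified as IMT-related or non-IMT-related". Study Oversight makes the committee's cardiologists "responsible for the review of the in-hospital course and follow-up adverse events of the participants", and Follow-Up provides "Participants will be followed by two experienced researchers every week through phone interviews after discharge". Neither is restricted to one arm.
- **Session rule.** Feasibility, a secondary endpoint, covers adverse events, heart rate and blood pressure, and says that "oxyhemoglobin saturation of patients during training while in hospital will be recorded". It adds that "the Borg scores will be recorded after every day of training in the hospital".
- **Who has sessions.** In the intervention section, the IMT group trains "twice a day, with an initial load of 30% of MIP", beginning 12 to 24 h after primary PCI. Controls receive standard care, "which included risk stratification, continuous monitoring and specific nursing". No sham session or matched study observation is described for them.

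**The concern.** Angina, dyspnea and arrhythmia can be brief, and some depend on the patient being asked. Their count depends on how often someone looks and what is asked. If one arm has two extra structured looks a day during the acute phase, an excess of such events with IMT could come from detection alone. The bias would run against IMT.

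The session readings raise a second problem. The article states no resting value before the session and no counterpart in controls. A fast heart rate or low saturation during a session could then reflect the training, the infarction or the patient's usual level, and classification as IMT-related or not has little to lean on.

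This touches stated aims. Objectives counts the avoidance of adverse events among the measures of effectiveness, which is a between-arm question. The Discussion presents the trial as the first to assess safety and efficacy in this setting, and says it is unknown whether the hemodynamic effects of forced breathing lead to clinical events.

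**Working it through.** **The plan's own figure.** The article gives no adverse-event rate, length of stay or detection figure, so there is nothing to reproduce on this point. Its only calculation is the sample size for MIP: 2 × (1.960 + 0.842)² × 12² / 15² = 10.05, rounded up to 11 per group, and 11 / 0.80 = 13.75, rounded up to 14. Both stated figures reproduce and neither bears on this point.

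**Side-by-side reading, in-hospital period.**

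| Source of adverse events | IMT | Control |
|---|---|---|
| General recording of listed events | yes | yes |
| Committee review of in-hospital course | yes | yes |
| Monitoring as part of care | presumably yes (not stated by arm) | yes |
| Recording during training, twice a day | yes | none, by construction |
| Resting value before each session | not stated | not applicable |
| Vital signs and questions at matched times | not applicable | not stated |

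The arms differ in one added source. The difference is in intensity, not in whether events are counted.

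**Illustration 1: number of added observations.** Assumptions, none from the documents: a stay of 5 to 7 days; each session finds a minor background event with probability 1% to 2%; a fraction u of those events would otherwise have gone unrecorded. From the documents: 2 sessions a day and 30 patients per arm.

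- Sessions in the IMT arm: 5 × 2 × 30 = 300 to 7 × 2 × 30 = 420.
- Extra events = sessions × probability × u.
- u = 1: 300 × 0.01 = 3 to 420 × 0.02 = 8.4.
- u = 0.5: 1.5 to 4.2.
- u = 0: none.

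In monitored patients u could be small for arrhythmia or desaturation. It is more likely to be appreciable for symptoms that emerge only when the patient is asked.

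**Illustration 2: effect on an odds ratio.** Assume the same true rate p in both arms, full detection with IMT, and detection d in controls, with 30 per arm. Observed rates are p and p·d, and the spurious OR = [p/(1−p)] / [pd/(1−pd)].

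| p | d | Expected IMT events | Expected control events | Spurious OR |
|---|---|---|---|---|
| 20% | 100% | 6 | 6 | 1.00 |
| 20% | 80% | 6 | 4.8 | 1.31 |
| 20% | 60% | 6 | 3.6 | 1.83 |
| 20% | 40% | 6 | 2.4 | 2.875 |
| 40% | 100% | 12 | 12 | 1.00 |
| 40% | 80% | 12 | 9.6 | 1.42 |
| 40% | 60% | 12 | 7.2 | 2.11 |
| 40% | 40% | 12 | 4.8 | 3.50 |

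Worked line: p = 0.40, d = 0.60 gives (0.40/0.60) / (0.24/0.76) = 0.667 / 0.316 = 2.11.

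Both illustrations show only that, with 30 per arm, a difference of a few detected events is enough to change the impression. They do not estimate the bias in this trial.

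**The case against.** **The session recording serves feasibility.** It stands beside workload, Borg score and IMT-group satisfaction, which belong to one arm by nature. The safety analysis sorts events by relation to IMT, and Data Analysis names odds ratios only for pneumonia and MACE, leaving other endpoints to be compared as appropriate. This stands in part: no between-arm test of minor events is prescribed. But Objectives makes avoidance of adverse events a measure of effectiveness, and nothing keeps session-detected events out of an arm-by-arm table.

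**Controls are closely observed.** Participants are admitted to the cardiac intensive care unit and control care includes continuous monitoring. While that lasts, two 15-minute sessions may add little for rhythm or saturation. This stands, and narrows the point mainly to transient or prompted symptoms.

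**The article is condensed.** A pre-session reading or a control observation schedule may be in the full protocol or case report form. This also stands: one can say only that none is stated. That staff attend each session is likewise an inference; the Discussion says only that vital signs are supervised and names no arm.

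**A stronger reading.** A reader might infer that in-hospital events are sought in the IMT arm only, that controls offer no comparable count, or that the safety question cannot be answered at all. The documents do not support this. The general recording rule names no arm, the committee reviews all participants, and death, recurrent infarction and stroke hardly depend on session observation.

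**Conclusion.** The point holds as possible unequal ascertainment of minor in-hospital events. The extra layer in one arm follows directly from tying the recording to training. That it produces an excess with IMT is plausible but not certain. It concerns angina, dyspnea, arrhythmia and similar transient findings, together with session vital signs that have no stated resting or control reference. The comparison of death, recurrent infarction and stroke is unlikely to be affected.

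The size is unknown. The 3 to 8 extra events and the odds ratios of 1.31 to 3.50 rest wholly on assumed stay, yield, true rates and detection, and could shrink to no bias if routine monitoring finds the same events in controls. This is a cheap improvement to data collection and reporting, not an error that undermines the trial.

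**What to change.** 1. While participants are in hospital, transcribe heart rate, blood pressure and saturation for controls from existing monitoring at matched twice-daily times, and ask both arms the same symptom questions at those times.
2. In the IMT arm, record a resting value just before each session, so that changes during training can be read within the patient.
3. Add a field to each adverse-event record for how the event was found: training session, matched check, medical record, weekly call or day-30 visit.
4. Report between-arm adverse events from all sources and, alongside, from sources common to both arms. List session-detected events separately for the IMT arm as well.

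Do not remove session-detected events from the main safety table. Some may be caused by training, and restricting the comparison to common sources would hide them. The two tables together let a reader see how far an excess depends on the extra observation.

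The cost is modest additional data entry in both arms, one field per event and one extra table. Treatment and sample size are unchanged.

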##### Major Adverse Cardiovascular Events (MACE)

MACE will be defined as all-cause death, recurrence of myocardial infarction, or stroke at 30 days post-randomization.

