#### Data Analysis

Continuous data will be presented as mean ± standard deviation (SD) and we will use the Student's *t*-test or analysis of variance for comparisons between groups when the variables are normally distributed. Otherwise, we will present data as median and interquartile range and will use Wilcoxon rank-sum test for comparisons. Categorical data will be presented as percentages and χ^2^ test or Fisher's exact test will be selected for data comparison. For the study endpoints, pneumonia and MACE will be compared between the IMT group and the control group with the odds ratio (OR). Other endpoints will be compared between groups as appropriate. The SAS version 9.4 (SAS Institute, Cary, NC) will be used to perform our statistical analyses. *P* values will be 2-sided and *P* < 0.05 will be regarded as significant.

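### The end-of-study safety analysis requires an outpatient day, so patients who die before discharge drop out with all their events and early fatal harm is understated there

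*Protocol article*

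**What the plan says.** Under Assessment and Reporting of Adverse Events, the protocol article lists the events to be captured. All-cause death is among them, as are stent thrombosis, acute heart failure and arrhythmia, and they "will be recorded in detail during both the in-hospital and follow-up periods". The same paragraph then fixes who is analysed: "This safety analysis will be conducted at the end of our research among patients who had at least 1 day of outpatient safety data".

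On the start of exposure, the section headed Invention: IMT says: "IMT will be performed every day from 12 to 24 h after primary PCI".

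Three other places bear on early events, and none of them states an outpatient condition:
- Study Oversight: "The cardiologists will be responsible for the review of the in-hospital course and follow-up adverse events of the participants". A safety analysis is also planned at the 20th randomisation.
- Feasibility: adverse events, heart rate and blood pressure are listed together with saturation, and "oxyhemoglobin saturation of patients during training while in hospital will be recorded".
- Major Adverse Cardiovascular Events: "MACE will be defined as all-cause death, recurrence of myocardial infarction, or stroke at 30 days post-randomization". Data Analysis compares this endpoint between the arms by an odds ratio.

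**The concern.** A safety set should be fixed by randomisation or by first exposure. This one is fixed by a later outcome: the patient has to leave hospital and then supply outpatient data. Death before discharge makes that impossible, and death is the first event on the article's own list. The exposure of interest begins in the coronary care phase, so the patients removed were at risk under the intervention before they were removed.

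The rule also works against the rest of its own paragraph, which takes care to record in-hospital events and then excludes some of the patients who had them.

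Safety is part of the feasibility aim under Objectives, and the Discussion presents this as the first study of the safety of IMT in such patients during the acute period. With 30 patients per arm, a handful of deaths may be the whole safety signal. One report could then show deaths under MACE and none, or fewer, under adverse events.

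**Working it through.** The plan gives no figure for the safety analysis, so there is none to reproduce. The check is a reading of the rule, followed by an illustration of size.

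**Step 1: who is in the set.** The condition is on patients, not on events.

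| Patient | In the end-of-study safety set? | Where in-hospital events appear |
|---|---|---|
| Discharged, gives an outpatient day | Yes | Safety analysis, in-hospital events included |
| Dies before discharge | No | MACE, for death, infarction or stroke only |
| Still in hospital at day 30 | No | MACE, for infarction or stroke only |
| Discharged, no outpatient data | No | MACE, if the event is a component and its status is known |

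Events during supervised training in hospital are also recorded under Feasibility, and the safety committee reviews the in-hospital course.

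**Step 2: what no endpoint comparison picks up.** MACE has three components. Stent thrombosis, acute heart failure, arrhythmia, angina and dyspnea are on the adverse-event list but are not MACE components. If one of these precedes an in-hospital death, the death counts in MACE and the preceding event falls out of the end-of-study analysis. Feasibility does not fill this gap between arms, because it concerns events during training and controls do not train.

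**Step 3: how many patients could be lost.** Inputs: 60 randomised, 30 per arm (Abstract). In-hospital death rate p: not in the documents, so assumed at 2%, 5% and 10%.

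Expected number lost = 60 × p. Chance of losing at least one = 1 − (1 − p)^60.

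| Assumed p | Expected lost of 60 | Chance of at least one |
|---|---|---|
| 2% | 1.2 | 70% |
| 5% | 3.0 | 95% |
| 10% | 6.0 | 99.8% |

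This counts deaths only. Patients still in hospital at day 30, or without outpatient data, would add to it.

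**Step 4: what the report would show.** In-hospital deaths with assumed counts, everyone else supplying an outpatient day:

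| Assumed deaths, IMT vs control | All randomised | Set as written |
|---|---|---|
| 3 vs 0 | 3/30 (10%) vs 0/30; Fisher p = 0.24 | 0/27 vs 0/30 |
| 6 vs 0 | 6/30 (20%) vs 0/30; Fisher p = 0.024 | 0/24 vs 0/30 |

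The in-hospital death count in the set is zero in both rows, as it would be for any true count.

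**The case against.** The strongest reply is that early harm has other routes into the results, and this largely stands. In-hospital death, infarction and stroke count in 30-day MACE, which is compared between arms with no restriction stated. Non-fatal in-hospital events of anyone later discharged with outpatient data stay in the safety set. Training events and the in-hospital course are covered under Feasibility and Study Oversight. In the illustration of 3 versus 0 deaths, MACE would still carry 3/30 versus 0/30. A reader might infer from the rule that early harm of IMT cannot appear anywhere; the documents do not support that. One reservation: the article does not state the analysis set for MACE, so its use of all randomised patients is inferred from the absence of any condition.

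Two further readings are tempting and also go too far.
- A reader might infer that sorting events into IMT-related and unrelated replaces a comparison by arm. Neither section says so, and table layout may be left to the full protocol or analysis plan, which are not shown.
- A reader might infer that the review at the 20th randomisation comes too early, since the newest patients have little follow-up. That is a trade-off. If 60 patients accrue evenly over the five planned months (about 150 days), one enters every 2.5 days, and waiting 30 days would mean about 30 / 2.5 = 12 more randomised before the first review.

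It is also fair to say that the size rests on assumption: no death rate is given, and patients with unstable hemodynamics or ventricular aneurysm are excluded. None of this defends the rule itself, which is stated outright and is not a detail left open.

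**Conclusion.** The population rule is wrong as written. It conditions the safety set on a post-randomisation outcome and removes every patient who dies before discharge, together with the events that led to the death. It also removes those still in hospital at day 30 and those without outpatient data. In-hospital deaths in that analysis are zero by definition, so it understates early fatal harm and can contradict the trial's own MACE result. If exclusions differ between arms, the comparison of the remaining events is distorted as well.

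The exclusion follows from the wording alone and needs no assumption. How many patients it affects does: 1.2 to 6.0 of 60 at assumed in-hospital death rates of 2% to 10%. The fault is confined to the end-of-study adverse-event analysis. The primary endpoint is not touched, and fatal events remain within MACE on the natural reading of that endpoint.

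**What to change.** Under Assessment and Reporting of Adverse Events, delete the outpatient condition and define the safety population as all randomised patients. Count events from randomisation to day 30, in hospital and after discharge, and report them by arm. If an exposure-based set is preferred, use patients who started training in the IMT arm with all controls; all randomised patients is simpler because it treats both arms alike.

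The same section already calls for these events to be recorded, so no new data are needed. The cost is one sentence in the plan.

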### Statistical Analysis

#### Sample Size Calculation

Our sample size calculation was based on a previous study (20). The mean of the MIP difference between the experimental group and the control group was estimated to be 15 cm H_2_O, the standard deviation was 12 cm H_2_O, the significance level was α = 0.05 and the test power was 1-β = 0.8. The resulting required sample size for each group was 11. Considering our projected 20% attrition rate, the sample size of each group should be increased to 14. To better study the secondary endpoints, a total of 60 cases will be included in the final analysis.

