## Abstract

**Background:** Uncommonly high rates of pneumonia in patients with acute myocardial infarction (AMI) undergoing primary percutaneous coronary intervention (PCI) have been observed during recent years. Inspiratory muscle training (IMT) could reduce pneumonia in patients undergoing coronary artery bypass grafting and other cardiac surgeries. The relationship between IMT and AMI is unknown. Here, we describe the feasibility and potential benefit of IMT in patients at high risk for pneumonia with AMI who have undergone primary PCI.

**Methods:** Our study is a prospective, randomized, controlled, single-center clinical trial. A total of 60 participants will be randomized into an IMT group and control group with 30 participants in each group. Participants in the IMT group will undergo training for 15 min *per session*, twice a day, from 12 to 24 h after primary PCI, until 30 days post-randomization; usual care will be provided for the control group. The primary endpoint is the change in inspiratory muscle strength, the secondary endpoint included feasibility, pneumonia, major adverse cardiovascular events, length of stay, pulmonary function tests measure, and quality of life.

**Discussion:** Our study is designed to evaluate the feasibility of IMT and its effectiveness in improving inspiratory muscle strength in participants with AMI who have undergone primary PCI.

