### Randomization

A specific computer-generated, randomized number will be placed in a sealed envelope. Researchers will be blinded to the information in envelopes and will select consecutive envelopes to distribute to consecutive participants, thus randomly assigning them to either the IMT group (*n* = 30) or the control group (*n* = 30). See study flow Figure 1.

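### The plan randomises 60, projects 20% attrition and still counts 60 in the final analysis; for endpoints that need the day-30 visit its own figures give about 48

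*Protocol article*

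**What the plan says.** All references are to the protocol article.

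- **Abstract, Methods:** "A total of 60 participants will be randomized into an IMT group and control group with 30 participants in each group". The Randomization section repeats 30 and 30.
- **Sample Size Calculation, assumptions:** "The mean of the MIP difference between the experimental group and the control group was estimated to be 15 cm H_2_O". With this go an SD of 12 cm H2O, a 5% significance level and 80% power. The Data Analysis section makes the tests two-sided. The result is 11 per group.
- **Sample Size Calculation, attrition:** "Considering our projected 20% attrition rate, the sample size of each group should be increased to 14".
- **Sample Size Calculation, last sentence:** for the sake of the secondary endpoints, "a total of 60 cases will be included in the final analysis".
- **Primary Endpoint:** MIP is measured at baseline and 30 days after randomisation. Spirometry and the quality-of-life questionnaires follow the same two-point schedule.

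**The concern.** The paragraph starts by separating the number needed for analysis (11 per group) from the number to enrol (14 per group), with 20% attrition linking the two. One sentence later that distinction is gone: 60 is called the number analysed, although elsewhere 60 is the number randomised. For an outcome that exists only if the patient attends on day 30, three statements cannot all be true: 60 randomised, 20% lost, 60 analysed.

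What is at stake is the denominator. A reader will take 60 as the evaluable number for the primary endpoint and judge the trial's precision on it. The enlargement to 60 was made for the secondary endpoints, and two of these, spirometry and quality of life, also depend on the day-30 assessment.

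**Working it through.** **Inputs.** Difference 15 cm H2O, SD 12 cm H2O, α = 0.05, power 0.80, attrition 20% (Sample Size Calculation); two-sided tests (Data Analysis); 60 randomised, 30 per arm (Abstract, Randomization).

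**1. The plan's own figures.**

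- Normal approximation: n per group = 2(1.960 + 0.842)² × 12² / 15² = 2 × 7.85 × 144 / 225 = 10.05, rounded up to 11. This matches the plan. Exact power at 11 per group (noncentral t) is 79.6%, close enough to 80%.
- Attrition: 11 / (1 − 0.20) = 13.75, rounded up to 14. This also matches.

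**2. The same attrition applied to 60.**

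- 60 × (1 − 0.20) = 48, or 24 per arm. The shortfall against the stated 60 is 12 patients (20%).
- In reverse, 30 analysed per arm would need 30 / 0.80 = 37.5, so 38 per arm or 76 randomised. The plan randomises 60.

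**3. What the difference does to the primary endpoint.** With n per arm analysed and SD 12:

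- standard error of the difference = 12 × √(2/n);
- power for 15 cm H2O from the noncentral t distribution with 2n − 2 degrees of freedom and noncentrality 15 / [12√(2/n)];
- detectable difference = the difference at which that power equals 80%;
- 95% CI half-width = t(0.975, 2n − 2) × 12√(2/n).

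| | 24 per arm (48) | 30 per arm (60) |
|---|---|---|
| Standard error, cm H2O | 3.46 | 3.10 |
| Noncentrality for 15 cm H2O | 4.33 | 4.84 |
| Power for 15 cm H2O | 98.9% | 99.7% |
| Difference detectable with 80% power, cm H2O | 9.91 | 8.83 |
| 95% CI half-width, cm H2O | 2.013 × 3.464 = 6.97 | 2.002 × 3.098 = 6.20 |

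The 24 per arm expected is more than twice the 11 per group that the plan requires.

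**4. Which endpoints are affected.** MIP, spirometry and quality of life need the 30-day assessment. Length of stay is known from the hospital record. Pneumonia and MACE are recorded in hospital and followed after discharge, with weekly phone contact, so they do not depend on a day-30 MIP measurement.

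**The case against.** The strongest reply is that the sentence concerns the secondary endpoints, not MIP. The Discussion confirms that the size was calculated on inspiratory muscle strength and then enlarged for secondary endpoints, pneumonia above all. On that reading 60 is an enrolment target loosely described. Pneumonia, MACE and length of stay can all be compared in 60 patients as randomised. Nor does any claimed property fail: the plan promises 80% power for 15 cm H2O and states no power, precision or detectable difference at 60.

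Much of this stands. It limits the point to endpoints measured at the day-30 assessment, and it means that the 8.8 cm H2O and 6.2 cm H2O figures above are comparisons made here, not figures the plan claims. It does not rescue the sentence, which refers to the final analysis without limiting the endpoints and shares a paragraph with a 20% attrition rate. If it means enrolment, it should say so.

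A reader might go further and infer that the primary test will be run on completers only, that losses will be heavier in the arm that trains twice daily, and that the result will be biased. If, say, the lost 20% of IMT patients gained nothing over control, 15 cm H2O among completers would become 0.80 × 15 = 12 as randomised. The documents do not support this. The Data Analysis section names tests but no analysis set or missing-data rule, and an article commonly leaves these to the analysis plan or full protocol, which are not shown. Unequal attrition is conjecture. The Follow-Up section already asks all participants to return at 30 days, with no exemption for those who stop training.

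**Conclusion.** The point holds as an error in a stated number. For MIP, spirometry and quality of life, the plan's own inputs give about 48 analysed (24 per arm), not 60. This assumes that the projected 20% applies to the enlarged sample as it did to the calculated one, falls equally on both arms, and means no day-30 measurement. The power and precision figures also assume the planning SD of 12 cm H2O.

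The effect on the primary endpoint is minor: power for 15 cm H2O falls from 99.7% to 98.9%, still far above 80%. It would be wrong to infer that the trial is underpowered, that it needs more patients, or that its primary comparison is biased. The correction is worth making because the denominator is wrong as written and cheap to put right.

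**What to change.** Replace the last sentence of the Sample Size Calculation section with text along these lines:

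> 60 will be randomised (30 per arm). With 20% attrition, about 48 (24 per arm) are expected to have day-30 MIP, giving 98.9% power for a difference of 15 cm H2O, or 80% power for 9.9 cm H2O, at an SD of 12 cm H2O. Pneumonia, MACE and length of stay will be compared in all 60 as randomised.

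Do not extend the last statement to adverse events without reconciling it with the section on their assessment and reporting, which restricts the safety analysis to patients with at least one day of outpatient safety data.

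The cost is two or three sentences and a slightly less favourable stated figure. Only if the sponsor truly means 60 patients with day-30 data would recruitment have to change, to about 76 (38 per arm), and the primary endpoint does not require that.
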